#### 2.5.2. Statistical Methods

The analysis group will include participants who have received at least one TEA treatment. The main observation indicators, including the incidence rate of AEs and the treatment discontinuation rate, will be collected and analyzed without replacing the missing data. Continuous data will be represented using descriptive statistics, such as the number of participants, mean, and standard deviation, whereas categorical data will be presented as frequencies (N) or ratios (%). When necessary, a 95% confidence interval will be calculated. Unless otherwise specified, the statistical tests will be conducted using a two-sided significance level of 5%.

Student’s *t*-test will be used to compare normally distributed continuous variables and the Wilcoxon rank-sum test or Mann–Whitney U test will be used to compare non-parametric continuous variables between the patient groups with AEs and those without. A Shapiro–Wilk test and Kolmogorov–Smirnov test will be used to assess the normality of the distribution. The chi-square test (or Fisher’s exact test, when appropriate) will be used to compare dichotomous variables such as sex, the presence of comorbidities, and co-medications between the patient groups with and without AEs. Variables with *p* < 0.05 in the bivariate analysis or those considered clinically relevant will be included in the final regression model. The Kaplan–Meier method will be used to analyze the incidence of AEs and Cox proportional hazards regression will be used to analyze the differences in the incidence of AEs between subgroups including demographic characteristics, TEA materials or procedures.

All AEs collected in the study will be categorized according to the SOC and PT as defined in the MedDRA. The incidence and incidence rates will be presented by PT; however, multiple occurrences of the same AE by PT in the same subject will be considered as a single event. Furthermore, different discovered severities and causalities for the same AE will be treated as the maximum severities and causalities, respectively. Moreover, AEs associated with TEA and SAEs will be presented as events.

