### 2.5. Statistical Analysis

#### 2.5.1. Sample Size Calculation

This prospective observational study will be conducted in a real-world clinical setting involving a diverse patient population with various diseases and clinical backgrounds. Given the expected high heterogeneity of the participants and high variance in the data, statistical sample size calculations are challenging. A previous study reported the incidence of AEs following TEA [38]; however, the data were based on published randomized controlled trials and case reports rather than actual clinical practice. To address these limitations, the sample size for this study was conservatively estimated at 12%, based on preliminary pilot data (unpublished). Using a margin of error of ±3.5% and a confidence level of 95%, the sample size calculation was performed. Accounting for an expected 5% dropout rate, the study aims to recruit approximately 350 participants.$$n^{*}=\mathrm{pq}\frac{{\left(Z_{\alpha /2}\right)}^{2}}{d^{2}}=0.12\times (1-0.12)\times \frac{1.96^{2}}{0.035^{2}}=331.2,\;n=\frac{n^{*}}{\left(1-\omega \right)}=\frac{331.2}{0.95}\approx 349$$

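### Student's pooled t-test is named for groups expected to split about 42 to 308, so its mean comparisons and screening p-values are miscalibrated if the group variances differ; Welch's test avoids this at a small cost in power.

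*Protocol article*

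**What the plan says.** Section 2.5.2 of the protocol article sets out how patients with AEs are compared with those without. Student's t-test "will be used to compare normally distributed continuous variables and the Wilcoxon rank-sum test" or the Mann–Whitney U test serves non-normal ones. Normality is to be checked with the Shapiro–Wilk and Kolmogorov–Smirnov tests. The section mentions neither a check of the variances nor an unequal-variance version of the t-test. Tests are two-sided at 5%.

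The p-values are put to use: variables with p < 0.05 "in the bivariate analysis or those considered clinically relevant will be included in the final regression model".

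The article does not state the sizes of the two groups, but they follow from Section 2.5.1, which plans on a 12% AE incidence from unpublished pilot data and says that "the study aims to recruit approximately 350 participants".

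**The concern.** The groups are formed by the outcome, so nobody controls their sizes, and at 12% incidence one is about seven times the other. The pooled t-test tolerates unequal variances well when groups are similar in size and poorly when they are not. If the smaller group is the more variable one, the pooled standard error is too small and the test rejects equal means too often. If the smaller group is the less variable one, the standard error is too large and real differences in means are missed.

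This matters because the study also aims to find patient, practitioner and intervention factors linked to AEs. The bivariate p-value is one of two routes by which a continuous factor reaches the final regression model, and the mean comparison is itself a result that readers will use.

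**Working it through.** **Inputs.** From Section 2.5.1: incidence 12%, margin ±3.5%, 95% confidence, 5% dropout, about 350 recruited. From Section 2.5.2: Student's t-test at two-sided 5%. Assumed, because the article gives no group SDs: r, the SD in the AE group divided by the SD in the no-AE group, from 0.5 to 2.

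**The plan's own figure.** n* = 0.12 × 0.88 × 1.96² / 0.035² = 331.2, and 331.2 / 0.95 = 348.6, so 349. This reproduces.

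**Group sizes.** 0.12 × 350 = 42 with AEs and 350 − 42 = 308 without. After 5% dropout (about 332 patients) the split is about 40 to 292.

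**Formula.** Set the no-AE SD to 1, n₁ = 42, n₂ = 308.
- Variance the pooled test assumes for the mean difference: s²(1/n₁ + 1/n₂), with s² = [(n₁ − 1)r² + (n₂ − 1)] / (n₁ + n₂ − 2).
- True variance: r²/n₁ + 1/n₂.
- Large-sample rejection rate under equal means: 2Φ(−1.96 × √(assumed / true)).

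**Example, r = 1.5.** s² = (41 × 2.25 + 307)/348 = 1.147. Assumed variance = 1.147 × 0.02706 = 0.0310. True variance = 2.25/42 + 1/308 = 0.0568. The square root of the ratio is 0.739, the effective critical value is 1.96 × 0.739 = 1.449, and the rejection rate is 14.7%.

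**Example, r = 0.67.** s² = (41 × 0.449 + 307)/348 = 0.935. Assumed variance = 0.0253. True variance = 0.0139. The square root of the ratio is 1.347, the effective critical value is 2.641, and the rejection rate is 0.8%.

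**Simulation** (normal data, equal means, 200,000 replicates per setting, 42 vs 308):

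| SD ratio r | Student's t | Welch's t |
|---|---|---|
| 0.5 | 0.1% | 5.0% |
| 0.67 | 0.8% | 5.0% |
| 0.8 | 2.1% | 5.1% |
| 0.9 | 3.4% | 5.0% |
| 1.0 | 5.0% | 5.0% |
| 1.1 | 6.8% | 4.9% |
| 1.25 | 9.7% | 5.0% |
| 1.5 | 14.6% | 5.0% |
| 2 | 23.0% | 5.0% |

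The 40 vs 292 split gives essentially the same results.

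**Is the imbalance the cause?** With 175 vs 175, Student's test stays at 5.0% for r = 0.67 and r = 1.5. With 70 vs 280 (20% incidence) it gives 1.4% and 12.1%; with 105 vs 245 (30%), 2.2% and 9.3%. A higher incidence than planned softens the problem but does not remove it.

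**Power, 42 vs 308, differences in units of the no-AE SD.**
- r = 0.67, difference 0.3: about 46% Student, 71% Welch.
- r = 0.8, difference 0.47: 87.0% Student, 92.5% Welch.
- r = 1, difference 0.40: 68.0% Student, 66.5% Welch; difference 0.465: 80.4% and 79.2%.
- r = 1.25, difference 0.47: 75.0% Student, 63.0% Welch. Student's apparent gain here comes from a test running at about 10% rather than 5%.

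**The case against.** The strongest objection concerns what the error rates mean. A reader might infer that unequal variances will let unrelated factors flood the regression model. The design does not support that. The groups are defined by AE status, so a variable wholly unrelated to AEs has the same distribution in both groups, variance included, and the pooled test then holds 5% at any split. Equal means with unequal variances is itself an association. For normal data, the log-odds of an AE change by x²(1 − 1/r²)/2 at x SDs from the mean, so the odds at ±2 SD are about 2.0, 3.0 and 4.5 times those at the mean for r = 1.25, 1.5 and 2. Such a variable is no false factor in the broad sense. This objection stands. What it leaves is a wrong p-value for the question a t-test answers, whether the means differ, and lost sensitivity when the AE group is less variable.

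Other points also stand:
- The SD ratios are assumptions. Section 2.5.1 expects heterogeneity among participants overall, which says nothing about AE against no-AE patients. Between 0.9 and 1.1 the distortion is small.
- Clearly skewed variables, as the number of insertions may be, should go to the rank test under the article's own normality rule and never meet the t-test.
- Clinically relevant variables may enter the model whatever their p-value, and the main indicators do not use this test.
- Welch's test is not free when variances are equal.

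One point stands only in part. The article never writes equal variances, and an analysis plan that is not shown could specify Welch's version. But the test it names is ordinarily the pooled one, so this is a named choice that can be improved, not a missing detail.

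**Conclusion.** The point holds, as a minor one. With the article's own 12% and 350, the named test is applied to groups of about 42 and 308, where its level depends heavily on equal variances. Under assumed SD ratios the error of the equal-means test is 3.4–6.8% at 0.9–1.1, about 10% at 1.25, 15% at 1.5 and 0.8% at 0.67. Welch's test stays at 4.9–5.1% throughout. In the last case Student's test finds a 0.3 SD difference about 46% of the time, against 71%.

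These figures rest on normal data, the planned incidence and SD ratios that the article does not give, so the actual distortion is unknown. The consequence is confined to reported mean comparisons and to the p < 0.05 screen for continuous variables. The documents do not support the stronger reading that the plan will generally admit false factors, nor any doubt about the AE incidence estimate or the sample-size calculation.

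**What to change.** In Section 2.5.2, replace Student's t-test with Welch's t-test for normally distributed continuous variables. The planned normality checks and the rank-based alternative can stay; nothing here bears on them. If an analysis plan already specifies the unequal-variance version, the article's wording only needs to match it.

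The cost is one word of text and, when the variances are in fact equal, about 1 to 1.5 points of power (for example 79.2% instead of 80.4%). No extra data or participants are needed.

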### 2.4. Data Collection

#### 2.4.1. Baseline Data

Demographic information, vital signs, medical history, concomitant medication and treatment details will be collected for each participant at the start of the study. This includes patient factors (age, sex, height, weight, blood pressure, pulse, body temperature, medical history, AEs of TEA within one year, medication history within one week, and concomitant medications or treatments), practitioner background factors (length of practice, affiliations, and board certification), and intervention factors (target disease, product manufacturer, thread material, thread shape, thread size, treatment area, number of needle insertions, needle length, needle thickness, and needling depth).

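### Admitting risk factors to the final model on bivariate p<0.05 gives a substantial chance of false factors; separately, about 40 expected patients with AEs mean that real effects are often missed and tend to be overstated

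*Protocol article*

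**What the plan says.** Section 2.5.2 (Statistical Methods) compares patients with and without AEs one variable at a time. Variables with p<0.05 "in the bivariate analysis or those considered clinically relevant will be included in the final regression model". The same section says that, unless otherwise specified, "the statistical tests will be conducted using a two-sided significance level of 5" percent. It states no multiplicity adjustment, shrinkage or limit on model size.

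Section 2.4.1 (Baseline Data) lists the factors collected in three groups: 11 patient, 3 practitioner and 10 intervention factors. The intervention group is target disease, product manufacturer, "thread material, thread shape, thread size, treatment area, number of needle insertions, needle length, needle thickness, and needling depth".

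Section 2.5.1 (Sample Size Calculation) sizes the study for the precision of one proportion, taken as 12% from pilot data: "Accounting for an expected 5% dropout rate, the study aims to recruit approximately 350 participants". Sections 1 and 2.4.3 make the factors associated with AEs an aim and part of the outcomes. The Discussion expects the risk profiles to inform practice and, for regulators, guidelines.

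**The concern.** The rule uses the same data twice. Many factors are tested one at a time at 5%, those that pass are refitted together, and the refitted p-values are again read at 5%. A factor that passed by chance has, by construction, an apparent association in these data, and refitting seldom removes it.

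Two further consequences have a different cause. With few AE patients, only large estimates reach p<0.05, so a real but moderate effect is usually missed, and when it is selected its estimate tends to be too large. A confounder that is not significant alone is left out unless someone adds it as clinically relevant. This matters here because treatment area plausibly follows target disease.

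The list of risk factors is at stake. A thread, depth or practitioner factor reported in error could misdirect practice.

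**Working it through.** **1. The plan's own figure.** n* = 0.12 × 0.88 × 1.96² / 0.035² = 331.2, and 331.2 / 0.95 = 348.6, which rounds up to 349. The stated calculation is reproduced and is correct for its purpose.

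**2. Expected patients with an AE.** The 12% is read as the proportion of patients with at least one AE; the text does not label it.
- 0.12 × 331.2 = 39.7; 0.12 × 350 = 42.0.
- Over 12% ± 3.5%, with 332 patients: 0.085 × 332 = 28 to 0.155 × 332 = 51.

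**3. Candidates.** 11 + 3 + 10 = 24 collected factors. AE patients per candidate: 39.7 / 24 = 1.7 (range 1.2 to 2.1 for 28 to 51 events).

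**4. False selection when no factor has an effect.** The expected number passing is 24 × 0.05 = 1.2. The chance of at least one, for k independent tests, is 1 − 0.95^k:

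| Candidates screened (k) | Chance of at least one false factor |
|---|---|
| 10 | 40% |
| 15 | 54% |
| 20 | 64% |
| 24 | 71% |

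The event count does not enter this formula.

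**5. Does the final model remove them?** Simulation: 332 patients, 12% with an AE, 24 null candidates (half binary, half continuous), bivariate screen at 5%, then a multivariable logistic model; 1,500 runs.

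| Candidates | At least one passes the screen | At least one still p<0.05 in the final model |
|---|---|---|
| Independent | 73% | 70% |
| Correlated, rho 0.3 | 63% | 46% |

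**6. Real effects.** Take 40 events, a factor split 50:50, and the normal approximation for a log hazard ratio: standard error = 1/√(40 × 0.25) = 0.316. The estimate must exceed exp(1.96 × 0.316) = 1.86 to reach p<0.05.

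| True hazard ratio | Chance of selection | Average (geometric mean) when selected |
|---|---|---|
| 1.5 | 25% | 2.24 |
| 2.0 | 59% | 2.46 |

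The logistic simulation with independent candidates shows the same pattern: a true odds ratio of 1.5 has a median of 2.41 when selected, and 2.0 a median of 2.59.

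**7. Dependence on the assumed structure.** With one true factor (odds ratio 1.4 per SD) and 23 null factors, a null factor was significant in the final model in 61% of runs when candidates were independent, and the true factor averaged about 1.6 when selected. With correlated candidates (rho 0.3) these became 30% and about 1.4. Exaggeration is therefore a tendency, not a certainty.

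**The case against.** The strongest reply is that the factor analysis is secondary and exploratory. Section 2.4.3 puts AE incidence, nature and severity first, the Introduction speaks of exploring factors, and the limitations disclaim proof of causality. This stands as to weight: the incidence estimate is untouched. It does not cover the rule itself, which is written as the entry criterion for the final model and tested at 5%.

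Several stronger readings are tempting, and the documents do not support them:

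- **That false factors follow from having only 40 events.** They follow from the number of tests and the 5% level. The event count governs power and exaggeration only.
- **That the list will usually contain a false factor.** The 71% needs all 24 collected factors to be screened and to be independent. Section 2.5.2 names only examples, and thread, needle, area and indication are likely to be related, which lowers the figure.
- **That the model has less than one event per parameter.** Counting the listed categories (section 2.3 gives 14 target indications and 8 areas, among others) gives about 50 candidate degrees of freedom, but nothing says that they enter one model.
- **That leaving clinical relevance undefined is itself an error.** Naming those variables can be left to an analysis plan that is not shown, and this route can bring in confounders that fail the screen. It does not undo the screen, because every variable with p<0.05 still enters.

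**Conclusion.** The point holds. As written, the screen gives a substantial chance of at least one false risk factor: up to 71% with 24 independent candidates, 40% with 10, and 46% still significant in the final model with 24 null candidates at rho 0.3. Separately, about 40 AE patients (1.7 per candidate) mean that moderate real effects are often missed and tend to be overstated when selected.

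This rests on three assumptions: all or most of the factors in section 2.4.1 are screened, 12% is a patient-level AE incidence, and correlation among candidates is no stronger than the values tried. The fault lies in a rule that the article states, not in detail left to a later document. It affects the stated aim on risk factors and not the main AE incidence estimate, so it should be changed but does not threaten the study's main result.

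**What to change.** In section 2.5.2, delete p<0.05 in the bivariate analysis as an entry rule. Before database lock, choose one of two routes:

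- **Short list.** The investigators name about 4 to 5 parameters in total and fit them whatever their p-values. Indication is collapsed to a few groups and counted within that total. With 39.7 events this gives 39.7 / 5 = 7.9 to 39.7 / 4 = 9.9 events per parameter. For four parameters, the chance of at least one false factor under independence is 1 − 0.95^4 = 18.5%, against 71% for 24.
- **Penalised model.** Fit all candidates in one ridge-penalised model and do not read individual p-values as confirmatory. Fitting all candidates in one model and testing each at 5%, with a Firth correction for example, would not help: that is still 24 tests.

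Under the short-list route, report every other factor as an unadjusted estimate with a 95% confidence interval, labelled exploratory.

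The cost is a change of analysis wording only; recruitment, data collection and care stay as they are. The downside is that fewer factors carry a formal conclusion.

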This multicenter, prospective, observational study aims to address this gap by evaluating the safety of TEA. Previous studies have primarily focused on traditional acupuncture, which has been reported as safe in several large-scale sample surveys [32]. However, TEA, being a unique and more invasive form of acupuncture, requires a more comprehensive evaluation of its safety profile. This study aims to examine AEs associated with TEA and explore how patient-, practitioner-, and intervention-related factors influence these events, ultimately contributing to a better understanding of TEA’s safe practice.

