## 2. Methods

### 2.1. Study Design, Setting and Aim

This multicenter, prospective, observational study will evaluate the safety of TEA in clinical practice. The study protocol is registered with the Clinical Research Information Service (CRIS; https://cris.nih.go.kr, (accessed on 16 December 2024); registration number KCT0008912). Participants will be recruited from three university-affiliated hospitals and two traditional Korean medicine clinics in Korea. Patients receiving at least one TEA treatment in a real-world setting, in line with the eligibility criteria, will be enrolled, and all AEs occurring in participants for a total of 3 months will be prospectively collected. In clinical practice, each patient will receive an appropriate number of TEA treatments based on their disease and condition; therefore, all additional TEA treatments after the first treatment will be collected as V2 to Vn in this study. Data regarding all TEAs received by participants and all AEs occurring during the study period will be collected and evaluated. The study procedure and assessment protocol for this trial are presented in Figure 1 and Table 1.

This study aimed to prospectively evaluate and validate the safety of TEA in real-world clinical practice. This observational approach enables the collection of safety data from a diverse patient population to reflect the complexities of actual clinical practice.

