#### 2.4.2. AE Monitoring

Definition of AEs [34]: AEs are defined as any unfavorable or unintended signs, symptoms, or diseases temporally associated with the TEA procedure.

Monitoring Schedule: Patients will be monitored at baseline (V1: enrollment period and first TEA treatment), 1 week post-treatment (V1 + 7D), 1 month post-treatment (V1 + 1M), 3 months post-treatment (V1 + 3M), and during intermediate procedures performed within 3 months post-treatment (evaluated 1 week later—Vn + 7D). In addition, participants will be encouraged to self-report AEs at any time during the study period using an application or diary. Symptom confirmation and evaluation will be conducted on the designated assessment dates.

All symptoms will be independently assessed by an investigator blinded to the specific TEA details and subsequently confirmed for AEs by the practitioner who performed the TEA to ensure that no AEs are omitted that are unrecognized by the patient or the blinded assessor. Patients will also be encouraged to voluntarily upload photos of AEs to the self-reporting application if they would prefer, so that they can be independently assessed by blinded researchers and medical staff. In addition, depending on the AE, appropriate medical examination and management, including laboratory tests and imaging, will be applied until the AE resolves.

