#### 2.4.3. Outcome Measures

The development of a standardized AE-reporting form is essential to facilitate accurate data collection, improve the quality of post-medical treatment, and ensure patient safety. The Medical Dictionary for Regulatory Activities (MedDRA) is a standardized international lexicon that is used by regulatory authorities for data related to medical treatments [35]. In the present study, the safety information report was developed based on the integration of MedDRA system organ class (SOC) and preferred term (PT) and a Delphi, a well- structured technique using collective consensus of multiple clinical experts [36]. Symptoms that may be associated with TEA are presented in Table 2.

Causality is assessed by evaluating the following causal factors according to the WHO-UMC criteria [37], which are the most widely used worldwide.

Is there a temporal relationship between the TEA and the occurrence of the AE?Does the same AE occur if TEA is repeated?Is it possible that the patient’s underlying medical condition or concomitant medication or procedure is the cause?Has the same AE been reported in the past?Did the AE improve after TEA was stopped?Is there a reasonable biological relationship between the procedure and the AE?

The outcome measure is the incidence, nature, and severity of AEs associated with TEA. During the 3-month post-treatment period, the incidence of AEs and rate of TEA treatment discontinuation due to AEs will be assessed. In addition, patient-, practitioner-, and intervention-related factors associated with the occurrence of AEs will be examined. The Standard Protocol Items: Recommendations for Interventional Trials (SPIRIT) schedule of enrollment, interventions, and assessments is shown in Table 1. The SPIRIT Checklist can be found in the Supplementary Files.

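### The aim and outcome are AEs associated with TEA, but the risk-factor analyses in section 2.5.2 use AEs without a causality restriction, so AEs judged unrelated count as events

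*Protocol article*

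**What the plan says.** The Introduction states the aim: "This study aims to examine AEs associated with TEA and explore how patient-, practitioner-, and intervention-related factors influence these events". Section 2.4.3 gives the outcome in the same terms: "The outcome measure is the incidence, nature, and severity of AEs associated with TEA". It also requires a causality grade: "Causality is assessed by evaluating the following causal factors according to the WHO-UMC criteria". The listed questions include whether the patient's underlying condition, or a concomitant medication or procedure, could be the cause.

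The same section then words the factor objective without that qualifier: "patient-, practitioner-, and intervention-related factors associated with the occurrence of AEs will be examined".

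The AE definition in section 2.4.2 is temporal only: "AEs are defined as any unfavorable or unintended signs, symptoms, or diseases temporally associated with the TEA procedure". It sets no time window, and section 2.1 says that "all AEs occurring in participants for a total of 3 months will be prospectively collected".

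Section 2.5.2 splits patients into those with and without AEs for the t, rank and chi-square tests and applies Kaplan-Meier to the incidence of AEs. For the regression it says "Cox proportional hazards regression will be used to analyze the differences in the incidence of AEs between subgroups including demographic characteristics, TEA materials or procedures". It refers to TEA-associated AEs once, as a category of their own: "Moreover, AEs associated with TEA and SAEs will be presented as events". It also says that conflicting causality grades for the same AE are resolved to the maximum, but it does not carry the grade into the factor analyses.

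**The concern.** The event in the factor analyses is not the event named in the aim and outcome. Under the wording of section 2.5.2, an intercurrent illness in week 8 that is graded unrelated puts the patient in the with-AE group and sets the Cox event time.

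This can mislead in two directions. Truly unrelated events should not depend on thread material, insertion depth, treatment area or practitioner, so counting them pulls those effects towards no effect. They do depend on background health. Comorbidity and co-medication are named among the variables to be tested, and p < 0.05 admits a variable to the final model. Such a factor could therefore be reported as a TEA risk factor when it only marks general illness. The Discussion expects the results to guide safer practice and regulatory standards, so a wrong list of risk factors would have consequences.

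The point concerns the event in the factor analyses only. It does not concern the reporting of overall incidence by MedDRA term.

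**Working it through.** **The plan's own figure.** Section 2.5.1: 0.12 × 0.88 × 1.96² / 0.035² = 331.2; 331.2 / 0.95 = 348.6, so 349, with about 350 recruited. This reproduces and does not depend on the point raised here. Evaluable patients: 350 × 0.95 = 332.5, or about 166 per group for a factor split evenly.

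**Inputs.** From the article: 12% AE incidence, 5% dropout, two-sided 5% level. Assumed: TEA-associated AEs in 7% vs 17% across the two levels of a factor (mean 12%), and unrelated AEs with probability u, independent and equal in both groups.

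**Dilution.**
- Any-AE risk: p = 1 − (1 − related)(1 − u).
- Hazard ratio: ln(1 − p₂) / ln(1 − p₁). Without unrelated AEs, ln(0.83) / ln(0.93) = 0.1863 / 0.0726 = 2.57.
- Power, two-proportion normal approximation: Φ[(d − 1.96·√(2p̄(1 − p̄)/n)) / √(p₁(1 − p₁)/n + p₂(1 − p₂)/n)], with d = p₂ − p₁, p̄ their mean and n = 166. For u = 0: (0.10 − 1.96 × 0.0357) / 0.0352 = 0.85, so power is 80%.
- Share of with-AE patients who have only unrelated AEs: 0.88u / p̄.

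| u | any-AE risk | hazard ratio | power | only unrelated |
|---|---|---|---|---|
| 0 | 7.0% vs 17.0% | 2.57 | 80% | 0% |
| 2% | 8.9% vs 18.7% | 2.23 | 74% | 13% |
| 5% | 11.7% vs 21.2% | 1.92 | 65% | 27% |
| 10% | 16.3% vs 25.3% | 1.64 | 52% | 42% |
| 20% | 25.6% vs 33.6% | 1.38 | 36% | 59% |
| 30% | 34.9% vs 41.9% | 1.27 | 26% | 69% |

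The last two rows are an upper bound, not an expectation.

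**If the planned 12% already means any AE.** Suppose a quarter of the hazard is unrelated and the true hazard ratio for related AEs is 2.0 in equal groups. In units of the average total hazard, the groups have related hazards of 0.5 and 1.0, plus 0.25 unrelated in each. The any-AE hazard ratio is 1.25 / 0.75 = 1.67. With 331 evaluable there are 39.7 events of any kind and 29.8 related. Power = Φ(√(events/4) × ln HR − 1.96) is 36% for any AE and 47% for related AEs. The analysis with fewer events is still the more powerful one.

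**False association.** Take a comorbidity with no effect on TEA-associated AEs (12% in both groups) but with different background illness, again with 166 per group:
- Unrelated 5% vs 10%: any AE 16.4% vs 20.8%, hazard ratio 1.30, p < 0.05 in about 18% of studies.
- Unrelated 5% vs 15%: any AE 16.4% vs 25.2%, hazard ratio 1.62, about 51%.
- Unrelated 10% vs 25%: any AE 20.8% vs 34.0%, hazard ratio 1.78, about 77%.

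The hazard ratios are ratios of 3-month cumulative hazards. If related AEs cluster early and unrelated ones do not, hazards for any AE are not proportional, and a Cox estimate would differ somewhat from these values.

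**The case against.** **The wording may be shorthand.** The outcome sentence says AEs associated with TEA, and the text then continues with plain AEs. The factor sentence in section 2.4.3 is also unqualified and so agrees with section 2.5.2. This stands in part: the document is inconsistent with itself, and the analysis section does not depart from every earlier statement. It does not remove the problem, because section 2.5.2 itself treats TEA-associated AEs as a category distinct from all AEs collected.

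**An analysis plan may define the event.** It may. But the point is not a missing detail: the event that the article names differs from the one in its aim and outcome.

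**The size is assumed.** This stands. No unrelated-AE rate is given, and the 12% is not stated to be TEA-associated. The Discussion reports that most pilot AEs occurred within 14 days, most often on the day of the procedure, which points to the low end of the range.

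**Restricting by causality has its own bias.** This also stands. The assessment asks about underlying conditions and co-medication, which are among the factors tested. A true TEA reaction in a patient with comorbidity may be graded down, so neither event definition is clean for those factors.

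**A stronger reading is tempting:** that the plan has deliberately fixed the event as any AE whatever its cause, and will therefore hide real risk factors or produce false ones. The documents do not support it. No sentence says that causality is to be ignored, nothing says that TEA-associated AEs will be presented only as events, and the harm depends on a rate nobody has stated.

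**Conclusion.** The inconsistency is in the text and should be resolved before analysis. Taken literally, section 2.5.2 counts AEs judged unrelated as events in analyses meant to find factors for TEA-associated AEs, and the temporal definition of an AE does not exclude them over 3 months.

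The direction of the bias is clear and its size is not. With 2% to 10% of patients having unrelated AEs, the loss in the worked contrast runs from modest (6 points of power) to substantial (28 points). The pilot description makes 20% to 30% unlikely. These figures rest on an assumed contrast, an even split, independence of related and unrelated AEs, and correct causality grading. The study is sized for the precision of an incidence estimate, and that calculation is unaffected.

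**What to change.** In section 2.5.2, define the event for the with/without-AE comparisons, Kaplan-Meier and Cox analyses as the first AE at or above a WHO-UMC category named in advance (for example, possible or higher). Use onset date as the event time, and do not censor patients at AEs judged unrelated. Report the same analyses for any AE alongside, and align the factor sentence in section 2.4.3 with this definition.

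The cost is a few sentences and a second run of the models. Causality and onset date are already in the schedule in Table 1. The downside is fewer events in the main factor analysis and reliance on a judged grade. Findings on comorbidity and co-medication should be interpreted from both analyses together. Naming the category now also prevents the event from being chosen after the results are seen.
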